**Fig. 1 Fig1:**
[figure not shown]
Standard Protocol Items: Recommendations for Interventional Trials (SPIRIT) schedule of enrollment, interventions, and assessments for the duration of the study. HCLF = High carbohydrate, low fat diet; KD= ketogenic diet, BMR = basal metabolic rate

**Fig. 2 Fig2:**
[figure not shown]
Timeline and details of study procedures

The principal investigator (PI) who is collecting the outcome measures will not be blinded to the diet allocation because feedback may need to be provided on a daily basis, to encourage dietary compliance. A researcher that will conduct the statistical analysis will, however, be blinded to the order in which the diets were undertaken.

### Participants

Twenty healthy individuals, between the ages of 18 and 50 years, will be asked to volunteer in this study. A total of 20 participants would provide 85% power to obtain a medium effect size for BMR (Cohen’s *d* effect size = 0.3) [54]. Using standardized and customized screening questionnaires for sleep quality and general health, volunteers will be screened to ensure that they are free from any chronic illness, depression, sleep disorders, for at least 6 months prior to the start of the study. Volunteers will be excluded if they are overweight or obese (BMI ≥ 26 kg/m^2^), have any adverse cardiac or metabolic conditions such as type 1 or 2 diabetes mellitus, hypercholesterolemia or hypertension confirmed by a clinician. The Pittsburgh Sleep Quality Index (PSQI) [55] and the General Health Questionnaire (GHQ) [56] will be used to assess quality of sleep and psychological health, respectively. Eligible participants will be asked to maintain the same level of physical activity throughout the study, which will be monitored using the standardized Global Physical Activity Questionnaire (GPAQ) [57]. If participants are taking a daily vitamin/mineral supplement, they will be asked to continue taking it as usual. If they are not taking any supplement they will be asked not to start taking one during the study. Using the dietary data obtained from 1 week of habitual dietary monitoring at the start of the study, daily calorie intake will be calculated for each participant and the total amount of calories consumed daily during both dietary interventions will be based on this value.

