## Methods

### Study design

The design of the study is a randomized controlled, cross-over trial. The study will follow the Standard Protocol Items: Recommendations for Interventional Trials (SPIRIT) guidelines for the design and conduct of a trial (Fig. 1; Additional file 1) [53]. As outlined in Fig. 2, participants will be asked to visit the Movement Physiology Research Laboratory on five occasions; the first visit will be for screening the volunteers to ensure that they fit the study criteria. Thereafter, eligible participants will return to the laboratory before the start of, and after, each dietary intervention. Following 1 week of normal habitual dietary monitoring, each participant will follow two isocaloric diets (a KD and a high-carbohydrate, low-fat (HCLF) diet) in a randomized order and separated by a 1-week washout period. Randomization of the order of the diets will be done using the Microsoft Excel 2010 (Version 14.0) CHOOSE and RANDBETWEEN functions. These functions (=CHOOSE(RANDBETWEEN(1,2), “A”,“B”) are able to assign each new participant into one of the two diets. Each dietary intervention will last for a minimum period of 3 weeks. In the KD it is critical for the participant to remain in a ketogenic state for three consecutive weeks. Should the participant leave the ketogenic state (as assessed by blood ketone levels), the dietary intervention period will be prolonged until the consecutive, 3-week ketogenic state is achieved. If a participant does not reach a ketogenic state in 2 weeks, we will exclude them, as it is indicative of non-compliance. However, we will be more lenient with someone who has entered a ketogenic state but may struggle to maintain the state, in which case we will guide them by closely monitoring their diet to ensure that their carbohydrate intake is suitably low and that their fat intake is suitably high. We will also look at the content of each participant’s diet to ensure that the foods do not contain imperceptible carbohydrates or that their protein content is not too high, which may result in gluconeogenesis. We will continuously encourage pure fat intake, e.g., cooking with olive oil, butter or coconut oil. Should a participant leave the ketogenic state more than five times they will be excluded from the study.

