### Outcomes

All outcomes will be measured at baseline, and before and after 3 weeks of each dietary intervention. The primary outcome will be diet-induced change in sleep quality, cognitive function, markers of inflammation and cardiovascular health status. The secondary outcomes will be a change in BMR and thyroid function.

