### Data analysis

Data analysis will be done using IBM SPSS Statistics (version 24, IBM Corporation, NY, USA). A two-tailed statistical significance will be accepted at *P* < 0.05. Each outcome variable assessed will be analyzed according to diet (KD or HCLF) and time (before and after each diet) using a repeated-measures two-way analysis of variance (ANOVA). Where appropriate, a Student-Newman-Keuls post-hoc test will be used to assess the origin of any significant differences detected by the ANOVA models. Variables will be adjusted for potential confounders which will be determined using multiple linear regressions. A power analysis has indicated that total of 20 participants would provide 85% power to obtain a medium effect size for BMR (Cohen’s *d* effect size = 0.3) [54].

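### The 85% power quoted for 20 participants at Cohen's d = 0.3 does not follow from the printed inputs, and it concerns BMR, a secondary outcome

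*Protocol article*

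**What the plan says.** The Participants section sets the sample size ("Twenty healthy individuals, between the ages of 18 and 50 years, will be asked to volunteer in this study") and supports it with one power statement: "A total of 20 participants would provide 85% power to obtain a medium effect size for BMR". The parenthesis that follows labels the quantity Cohen's d and gives its value ("effect size = 0.3"), with a literature reference. The Data analysis section repeats the statement ("total of 20 participants would provide 85% power to obtain a medium effect size for BMR") and adds no further input.

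The other relevant settings are:

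- Design: "The design of the study is a randomized controlled, cross-over trial". Each participant follows both diets and is measured before and after each one.
- Test level: "A two-tailed statistical significance will be accepted at *P* < 0.05".
- Model: a two-way repeated-measures ANOVA by diet and time, in Data analysis.
- Status of BMR: "The secondary outcomes will be a change in BMR and thyroid function", in Outcomes. The same section names sleep quality, cognitive function, inflammation markers and cardiovascular health status as primary.

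The article does not say which SD divides the difference to give d, what within-person correlation was assumed, or which test the power refers to.

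**The concern.** Twenty people, a standardised difference of 0.3 and 85% power look incompatible at first sight, even in a cross-over. The label *medium* adds to the doubt: it sits near f = 0.25 on the scale used for ANOVA and is an odd description of d = 0.3. This suggests that two effect-size scales may have been mixed.

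The statement is the article's only argument that 20 participants are enough. If it depends on an undisclosed and demanding correlation, or on an effect twice the size printed, a reader will overrate what the trial can detect for BMR. The reader also learns nothing about sensitivity for the outcomes the trial names as primary.

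**Working it through.** **Inputs.** n = 20 and d = 0.3 (Participants); two-sided alpha 0.05 (Data analysis); within-person comparison of two diets (Study design). The within-person correlation ρ is not stated, so it is varied below.

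**1. Attempt to reproduce 85%, with d as the standardised paired difference.** Write dz = mean difference / SD of the differences. The paired t-test has df = 19 and noncentrality dz × √n = 0.3 × √20 = 1.34. The critical value is 2.093. The noncentral t distribution gives power **24.7%** (normal approximation 26.8%). The stated 85% is not reproduced.

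Other tests at d = 0.3 do not reach it either:

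| Test | Power |
|---|---|
| Paired, one-sided, n = 20 | 36.3% |
| Two-sample, two-sided, 10 per group | 9.7% |
| Two-sample, two-sided, 20 per group | 15.2% |
| Two-sample, one-sided, 20 per group | 23.8% |

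Solving the paired formula the other way, 20 participants have 85% power at dz = 0.71 and 80% at dz = 0.66. At dz = 0.3, 85% needs 102 participants (101 give 84.8%) and 80% needs 90.

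**2. With d scaled by the between-person SD.** For a comparison of post-diet values, dz = d / √(2(1 − ρ)). For the difference between the two pre-to-post changes (the diet-by-time contrast), with equal correlation among all four measurements, dz = d / √(4(1 − ρ)).

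| ρ | dz, post-diet | Power | dz, diet × time | Power |
|---|---|---|---|---|
| 0 | 0.212 | 14.7% | 0.150 | 9.8% |
| 0.5 | 0.300 | 24.7% | 0.212 | 14.7% |
| 0.7 | 0.387 | 37.6% | 0.274 | 21.4% |
| 0.8 | 0.474 | 52.1% | 0.335 | 29.7% |
| 0.9 | 0.671 | 81.2% | 0.474 | 52.1% |
| 0.91 | 0.707 | 85.1% | 0.500 | 56.5% |

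Setting dz = 0.7065 (the unrounded value for 85%) and solving for ρ:

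- post-diet: ρ = 1 − (0.3 / 0.7065)² / 2 = 0.910
- diet × time: ρ = 1 − (0.3 / 0.7065)² / 4 = 0.955

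**3. With 0.3 read as Cohen's f.** This is not what is printed. For m repeated measurements in one group, the noncentrality of the F test is n × m × f² / (1 − ρ).

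| Measurements | Power at ρ = 0.5 | ρ needed for 85% |
|---|---|---|
| 2 | 72.1% | about 0.64 |
| 4 | 88.3% | about 0.455 |

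For two levels, f = d / 2, so f = 0.3 means d = 0.6. Check: with d = 0.6 and ρ = 0.64, dz = 0.6 / √(2 × 0.36) = 0.707, which gives 85%. The four-measurement version is a 3-df test of any difference among visits, not of the diet effect specifically. The two-level version does test the diet effect.

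**4. Which outcome the figure covers.** Both power sentences name BMR only, and Outcomes places BMR among the secondary outcomes. No power figure is given for any primary outcome.

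**The case against.** The strongest reply is that the article never says how d is standardised. A reader might infer from step 1 that the design simply has 25% power and that effects of the stated size would be missed three times in four. The document does not support that as a flat statement. The 25% holds only if 0.3 is scaled by the SD of the paired differences, or by the between-person SD with ρ = 0.5. On the between-person scale, 85% can be reached if ρ is high enough.

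A second reply is that 0.3 may be Cohen's f printed as d. The label *medium* and the planned repeated-measures ANOVA make that plausible, and 85% then needs only a moderate correlation. The fault would be a wrong label rather than a seriously underpowered trial. This remains an inference, since both places print d.

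Third, an article condenses its full protocol, so leaving out a correlation or an SD is not in itself an error. That is accepted. The point is that the numbers that are printed do not agree without such an input.

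Finally, a reader might infer that the trial claims 85% power for sleep, cognition or lipids. It does not; both sentences are limited to BMR.

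These replies make the 25% conditional. They do not rescue the sentence: either the effect size is mislabelled, or the 85% rests on a very high correlation that is not given.

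**Conclusion.** The point stands in this form: 85% power does not follow from n = 20, d = 0.3 and two-sided 5%. Its size depends on the scale of d:

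- **SD of the paired differences:** power is 25%, and 85% needs dz = 0.71 or 102 participants.
- **Between-person SD:** the figure holds only at ρ of about 0.91 (post-diet) or 0.955 (diet by time, assuming equal correlations). At ρ = 0.7, power is 38% and 21%.
- **Cohen's f, two levels:** the printed effect is half the one used (0.3 against d = 0.6), and ρ of about 0.64 is needed.

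The document does not show which of these applies, so it cannot be said that the trial's power is 25%. Whichever applies, the sole sample-size justification concerns a secondary outcome and covers none of the primary ones. All figures assume 20 completers.

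**What to change.** Keep n at 20. In both Participants and Data analysis, correct either the effect size or the power so that they agree. Name the test, the standardiser and the assumed within-person correlation, and drop *medium* for d = 0.3. If the calculation used Cohen's f, say so and give the matching d.

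If the original settings cannot be recovered, a replacement could read: *With 20 completers and a two-sided 5% level, the paired comparison has 85% power for a mean difference of 0.71 SD of the within-person differences (80% for 0.66); for 0.3 SD of the differences it has 25%.*

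Add that the calculation was made for BMR, a secondary outcome. Because this scale has no units, also state that the same detectable standardised difference applies to each primary outcome when it is tested alone by the same paired comparison.

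The change costs two sentences and no participants. The downside is that the stated sensitivity becomes less favourable.

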### Dietary intervention

Participants will, in a random order, follow a KD (15% carbohydrate, 60% fat, and 25% protein) and a HCLF diet (55% carbohydrate, 20% fat, and 25% protein). Each dietary intervention will last for a minimum of 3 weeks, with a 1-week washout period in between each diet, during which time participants will be asked to follow their habitual diet (as during the first week of the study). The PI will provide each participant with meal plans that are specific to each dietary intervention, but will maintain an identical calorie intake to that which was consumed, on average, over the first week of following each participant’s habitual diet. Therefore, the PI will formulate individualized meal plans with the correct respective macronutrient content for each dietary intervention according to each participant’s habitual calorie intake. The PI will also educate each participant on the fundamentals of each dietary intervention and provide foodlists, and other resources containing information on dietary macronutrient compositions and calories, to assist each participant to make food choices of their preference, but in line with the dietary intervention. The PI will also be easily assessable to each participant for guidance and/or advice, as well as motivation, throughout the study. Ultimately, these measures should assist with participant compliance.

### Dietary monitoring

Throughout the study (i.e., during the first week (habitual week), during both dietary interventions and during the washout period), participants will be asked to record a detailed account of their daily dietary consumption using specialized, but commercially available, calorie-counter applications (MyFitnessPal, version 7, Under Armour). The applications have the functionality to export detailed diet data for later analysis. In addition, the PI will be able to remotely monitor (smart devices will be connected), and critically analyze and assess, macronutrient composition and calorie intake, in order to provide each participant with daily feedback during the diets. The feedback provided will either be positive, encouraging comments, or advice on how to best amend their diet for the purpose of the study. In order to ensure that a nutritional ketosis is maintained for three consecutive weeks of being on the KD, blood levels of β-hydroxybutyrate (BOHB) will be determined using a finger-prick test and a β-ketone handheld analyzser (Freestyle Optium, Abbott Diabetes Care Ltd., United Kingdom). Levels of BOHB will be measured before and after each dietary intervention, as well as at the end of each week while participants are on the KD. During the intervention, each participant will be provided with a β-ketone handheld analyzer and shown explicitly how to use the device. Participants will then be able to monitor ketones at home themselves without having to return each week for laboratory assessment. Participants will be required to take a photo of the value recorded by the handheld analyzer and send that photo to the PI. Monitoring of BOHB levels will be done to confirm the ketogenic state in each participant, and once achieved, the BOHB assessment will be repeated every second day to ensure that the ketogenic state is maintained for three consecutive weeks. Maintenance of a ketogenic state for three consecutive weeks will be a critical requirement of the study. When participants leave the ketogenic state (considered as BOHB levels below 0.4 nM), the dietary intervention period will be prolonged until the consecutive 3-week ketogenic state is achieved.

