Further, it is important to note that even with an increase in calorie intake on a KD, a greater loss of body mass has been reported in overweight adolescents compared with those on the HCLF diet, and it has been suggested that a non-calorie restricted KD may be more effective than a very-low-calorie diet due a greater maintenance of metabolic rate, which is a consequence of a higher caloric intake [40]. Despite the most common application for the KD being a reduction in total body mass, there is astonishingly little research investigating the effects of a KD, compared with the conventional HCLF diet, on basal metabolic rate (BMR) or thyroid function [41, 42]. Changes in the thyroid hormones triiodothyronine (T3) and thyroxine (T4) that contribute to maintenance of metabolic rate due to a low-carbohydrate diet have produced mixed results [41–43]. Importantly, however, caloric intake in these studies was not controlled. Instead, greater loss of body mass on the KD compared with HCLF diets, in obese and/or overweight individuals, has been attributed to spontaneous reduction in caloric intake [41, 44, 45], reduced hunger and/or increased satiety due to increased fat consumption [46–49], or an inhibitory effect of β-hydroxybutyrate (BOHB) (the major circulating ketone body) on appetite [50]. Given the persistent metabolic adaptation that follows loss of total body mass and/or calorie restriction, namely adaptive thermogenesis, which promotes an overall decline in energy expenditure and a reduced BMR [51, 52], it is intriguing to determine whether diet composition, independent of a loss of body mass, caloric intake, and levels of physical activity, has any significant metabolic effects.

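### The only numeric ketosis cut-off, BOHB below 0.4 nM, carries an implausible unit; 0.4 mM (mmol/L), a million times higher, is almost certainly meant

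*Protocol article*

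**What the plan says.** Under Dietary monitoring, blood β-hydroxybutyrate (BOHB) "will be determined using a finger-prick test and a β-ketone handheld" meter, which participants use at home. Once ketosis is confirmed, the test is repeated every second day. The section states the cut-off and its consequence together: "When participants leave the ketogenic state (considered as BOHB levels below 0.4 nM), the dietary intervention period will be prolonged". It also says how much depends on the state: "Maintenance of a ketogenic state for three consecutive weeks will be a critical requirement of the study".

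The Study design section repeats the prolongation rule without a number, referring only to blood ketone levels. It adds two exclusion rules, also without a number: "If a participant does not reach a ketogenic state in 2 weeks, we will exclude them" and "Should a participant leave the ketogenic state more than five times they will be excluded from the study".

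The article gives no other BOHB threshold, no BOHB value in mM or mmol/L, and no display unit or resolution for the meter. The Background describes BOHB as "the major circulating ketone body".

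**The concern.** A nanomolar cut-off does not fit a substance that the article itself presents as the main ketone in blood, supplied as fuel in place of glucose and read from a finger-prick drop on a handheld device. Millimolar is the natural reading, but a reader cannot confirm it because no other passage restates the threshold.

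The figure is an operating rule. It formally decides when a KD period is extended, and so how long each participant is exposed. The two exclusion rules appear to rest on the same definition, although they do not cite the number. If so, it also affects who completes the trial. Taken at face value, the printed threshold would let almost every reading pass as ketosis. Anyone assessing adherence, or repeating the intervention from the published text, needs the correct value.

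**Working it through.** The cut-off is a stated constant that the article does not derive, so there is no calculation of the plan's to reproduce. The check is a unit conversion followed by a plausibility test.

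**Inputs from the article**
- Cut-off: 0.4 nM (Dietary monitoring).
- Testing every second day for three consecutive weeks, i.e. 21 days (Dietary monitoring).
- 20 participants (Participants).

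**Assumptions, not in the article**
- Non-ketotic blood BOHB somewhere in 0.02 to 0.3 mmol/L.
- A meter that displays mmol/L in steps of 0.01 to 0.1.

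**Step 1: size of the unit difference.**
- 0.4 nM = 0.4 × 10⁻⁹ mol/L = 4 × 10⁻⁷ mmol/L.
- 0.4 mM = 0.4 × 10⁻³ mol/L.
- Ratio = 10⁻³ / 10⁻⁹ = 1,000,000.

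**Step 2: would non-ketotic values fall below the printed cut-off?**

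| Assumed BOHB (mmol/L) | In nM | Multiple of 0.4 nM | Below 0.4 nM? | Below 0.4 mM? |
|---|---|---|---|---|
| 0.02 | 20,000 | 50,000 | no | yes |
| 0.05 | 50,000 | 125,000 | no | yes |
| 0.1 | 100,000 | 250,000 | no | yes |
| 0.3 | 300,000 | 750,000 | no | yes |

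Across the range, the printed unit labels every non-ketotic value as ketosis, while 0.4 mM labels every one as out of ketosis. For the printed unit to work, even the lowest assumed value would have to be too high by a factor of 50,000.

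**Step 3: would the intermediate prefix do?** At 0.4 µM, the same range (20 to 300 µM) is 20/0.4 = 50 to 300/0.4 = 750 times the cut-off, so it fails in the same way. Of nM, µM and mM, only mM separates the two states.

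**Step 4: could the meter resolve the printed cut-off?**
- A step of 0.01 mmol/L is 10,000 nM, and 10,000/0.4 = 25,000 times the cut-off.
- A step of 0.1 mmol/L is 100,000 nM, and 100,000/0.4 = 250,000 times the cut-off.

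The smallest non-zero display would already count as ketosis. Only a displayed zero could be read as below the threshold.

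**Step 5: how often is the rule consulted?** Testing every second day over 21 days gives 10 readings (days 2, 4, …, 20) or 11 (days 1, 3, …, 21). For 20 participants who complete the KD without a lapse, that is 20 × 10 = 200 to 20 × 11 = 220 readings. This counts how often the cut-off is used, not how many decisions are wrong.

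**The case against.** The strongest reply is that this is a misprint with little effect on conduct. Results reach the investigator as images: "Participants will be required to take a photo of the value recorded by the handheld analyzer and send that photo to the PI". The investigator would compare the displayed number with 0.4, and nobody would convert it to nanomolar first. Diet logs are reviewed daily as a second adherence check that does not depend on any ketone unit. The outcome definitions, power statement and analysis model do not use the figure. This stands, and it is why the point claims no wrong decisions.

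It is also fair that the physiological range and the display step are assumptions. Only the factor of 1,000,000 is firm. The multiples in Steps 2 and 4 illustrate how implausible the unit is and should not be read as effect sizes. Whether the literal rule could ever trigger depends on how the meter shows very low values, which the article does not say.

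The link to the two exclusion rules is an inference, since they name the ketogenic state but no number. One of them concerns reaching ketosis, whereas the printed number is attached to leaving it.

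None of this makes the printed unit right. Nor is it detail that an article may leave to a fuller document: the article chose to state the threshold and stated it wrongly. Other milli- units in the article, such as the 100-mm scales and the 10-ml blood sample, print normally, so a general typesetting fault is unlikely.

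**Conclusion.** The concern holds. As printed, the threshold for leaving ketosis is too low by a factor of 1,000,000 if millimolar was intended. That intention is inferred, because the article states no other unit. The inference rests on BOHB's described role, the finger-prick method and an assumed non-ketotic range of 0.02 to 0.3 mmol/L, and it is unchanged across that range. Applied literally, the prolongation rule would hardly ever trigger, and the exclusions that seem to depend on it could not do their job. In practice the effect is probably small. It should be corrected because it is the only numeric definition behind a condition the authors treat as essential.

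**What to change.** In the Dietary monitoring section, replace nM with the unit the handheld analyser displays, presumably mmol/L, so that the cut-off reads as below 0.4 mmol/L. The trial team should also confirm that this value, in this unit, was the one applied when KD periods were prolonged and when participants were excluded under the two Study design rules. The cost is one word and one confirmation. Design, sample size and analysis are unaffected.
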